The health issues associated with occupational and environmental risks are of major concern in low and middle income countries where many people live and work in proximity to polluted wastewater streams, waste processing plants and disposal sites. For people whose livelihoods depend on the collection, on sorting and on reusing of waste, measures to improve their daily working conditions and to reduce associated health risks are needed. Various guidance documents in the grey and peer-reviewed literature provide developing country-specific recommendations to reduce the exposure to potential hazards and integrated control measures along the waste chain (Bünger et al. 2000; Hoornweg 2000; Cissé and Tanner 2001; Cissé et al. 2002; Rushton 2003; Cointreau-Levine 2006; WHOa-b 2006; Drechsel et al. 2010; Stenström et al. 2011; Hoornweg and Bhada-Tata 2012). On the other hand formal and save waste recovery and reuse practices are very limited in the low and middle income countries and often done informally and associated with health concerns, especially when the waste is reused in agriculture and aquaculture (WHO 2006a-d). For example, a study conducted on farmers who use wastewater in India had excess prevalence and intensity of infection compared to a control group (egg counts/g faeces) of ascariasis (47% vs. 13% and 69% vs. 31%, repectively) and hookworm infection (69% vs. 31% and 62% vs. 35%, respectively). Moreover, a review of epidemiological evidence on the health effects of wastewater and excreta use in agriculture conducted by Blumenthal and Peasey (2002) highlighted significant risks of gastro-intestinal infections to people working and living along the WW and FS chains.

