Hence, we want to add on top of this study a more detailed approach to better understand the related health risks and disease outcomes (e.g. diarrhoea episodes, skin diseases, helminth and intestinal protozoa infections) potentially caused by the exposure to WW and FS. This includes following three approaches (Figure 1):

1. The cross-sectional survey has the aim to assess the existing exposure risks due to WW and FS in directly exposed groups (worker and farmers) and partially and non-exposed groups (communities) with a specific focus on parasitic infections, skin diseases, eye diseases, and diarrhoeal episodes. The cross-sectional survey comprises of two components: (i) a questionnaire study to obtain health risk and health outcomes (e.g. diarrhoeal episodes and skin and eye disease) related to the exposure to WW and FS; (ii) and the collection of stool samples to determine the prevalence and the intensity of parasitic infections. We will analyse the stool samples with the Kato-Katz technique (1 stool sample subjected to duplicate Kato-Katz thick smears) for helminth infections and the formalin-ether concentration technique (FECT) for intestinal protozoa infections. A sub sample of Ascaris-positive specimens will be fixed in ethanol pending polymerase chain reaction (PCR) exanimation for species identification (*A.lumbricoides, A.suum*) (Becker et al. 2012).
2. A pathogen flow analysis (PFA) to observe the variance of certain contamination parameters (e.g. faecal coliforms) at critical control points over time. Therefore, we will analyse existing operational monitoring data of NWSC on WW and FS and sample WW and FS for analysis of helminth eggs and intestinal protozoa cysts.
3. We will interlink the PFA with a QMRA to estimate diarrhoeal and parasitic infection risk and validate the simulated results with the findings of the cross-sectional survey. This will further help us to calculate specific exposure scenarios for different reuse practices for WW and FS and to compare the results with local and international health based targets (HBT).

[figure not shown]

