**Figure 3** Map of the area around the WW treatment plant ‘Bugolobi Sewerage Treatment and Disposal Works’ (BSTDW) and the Nakivubo swamp. Exposure groups are indicated with red squares. We assume that communities living approximately 2 km away from Nakivubo swamp and/or live ether east of the Port Bell road and west of Kibuli road and Tank Hill road are no longer exposed to wastewater and faecal sludge form BSTDE and Nakivubo swamp

- 1. Study designs
     1. Study design for objective 1

**Approach:** We will conduct a cross-sectional survey to assess and map the existing exposure risks due to WW and FS in directly exposed groups (worker and farmers) and partially and non-exposed groups (communities) with a specific focus on parasitic infections, skin diseases, eye diseases, and diarrhoeal episodes. The cross-sectional survey comprises of two components: (i) a questionnaire study to obtain health risk and health outcomes (e.g. diarrhoeal episodes and skin and eye disease) related to the exposure to WW and FS; (ii) and the collection of stool samples to determine the prevalence and the intensity of parasitic infections. We will analyse the stool samples with the Kato-Katz technique (1 stool sample subjected to duplicate Kato-Katz thick smears) for helminth infections and the formalin-ether concentration technique (FECT) for intestinal protozoa infections. A sub sample of Ascaris-positive specimens will be fixed in ethanol pending polymerase chain reaction (PCR) exanimation for species identification (*A.lumbricoides, A.suum*).

- - - 1. Study population

In the cross-sectional survey we will target in total five groups (three directly, one partially and one not exposed to WW and FS), namely: (i) workers operating the BSTDW (W1); (ii) workers collecting and transporting FS (W2); (iii) farmers working along the Nakivubo Channel and the wetland (F); (iv) community members who are exposed by WW and FS e.g. live in areas which are from time to time flooded but do no farming within the wetland (C1) and people therefore exposed to WW and/or FS; and (v) community members who live and work approximately 2 km away from the Nakivubo swamp, hence, we assume that these groups are not directly exposed to the WW and the FS (C2).

- - - 1. Sample size calculations

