To calculate the sample size we relied on the hypothesis 1. We conducted a logistic regression analysis having four exposure levels W1/W2, F1, C1 and C2. The highest exposure level is assigned to W1 and W2 (due to their daily exposure to raw and untreated WW and FS), the second highest to F (due to accidentally intake of contaminated water and soil), the third highest to C1 (e.g. due to frequent flooding events) and the lowest to C2 (Blumenthal and Peasey 2002; WHO 2006a). The number of persons in category W1 and W2 is assumed to be limited to 150, the number of F1 to 250, the number of persons in class C1 to 200 while the number of persons in class C2 could be as high as necessary (Table 1).

**Table 3** Selection criteria and potential numbers of exposure groups

| **No.** | **Definition of exposure group** | **Estimated number of individuals** |
| --- | --- | --- |
| 1. **W1** | Worker who operate and work at Bugolobi Sewerage Treatment and Disposal works | 30-50 |
| 1. **W2** | Worker who collect and transport the faecal sludge | 100-150 |
| 1. **F** | Farmers who working within the Nakivubo swap and are exposed to WW and/or FS | 250-500 |
| 1. **C1** | Community in proximity of the wetland but are no farmers | 10,000-20,000 |
| 1. **C2** | Community who live and work approximately 2 km away from the Nakivubo swamp and live ether east of the Port Bell road and west of Kibuli road and Tank Hill road. | 10,000-20,000 |

We aim at a power of 95%, in order to make sure that a reduction in effective exposure variance by 35% still leaves 80% power. Effective exposure variance is the variance of the 4-level exposure variable after regression on potential confounding variables (e.g. socio-economic status). With a variance reduction by 35%, the remaining exposure variance is 65% of the original value, so that the standard deviation after reduction is about 80% of the original exposure standard deviation. This increases the standard error by a factor of 1.25. If we have 80% power with the adjusted standard error (SE) 1.25*SE we may detect an effect of ln(odds ratio (OR)) = (1.96+0.84)*1.25*SE = 3.5*SE = (1.96 + 1.54)*SE. And 1.54 corresponds to slightly less than 95% power with the original unadjusted SE. Clearly, the factor limiting power most strongly is the relatively small size of the highest exposure group (W1, W2).

**Table 4** Results of the logistic regression analysis considering four exposure variable (C1, C2, F1 and W1)

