Further, we will conduct with each participant a questionnaire interview (will take about 30 min) to assess e.g. their demographic, occupation, intensity and causality of exposure to WW and FS, personal protective equipment, hygienic behaviour and signs and systems of specific health outcomes (ANNEX 10.1). Later, each participant will be provided with a small plastic container which is labelled with their unique ID. Participants will be invited to return the container with a fresh morning stool sample the following day directly to the working place for W1 and W2 and for community member and farmer to an appointed health centre. The anticipated study period for W1 will be 2 days, for W2 5 days, for F 10 days, for C1 5 days and for C2 10 days.

Table 6 Sampling framework for the cross-sectional study

| Exposure group | Total participants | Allocated working days | Selected unit | Participants per unit |
| --- | --- | --- | --- | --- |
| **Worker 1** | 50 | 2 | Excessive sample | 50 workers |
| **Worker 2** | 100 | 10 | Excessive sample | 100 workers |
| **Farmers** | 275 | 10 | 275 randomly selected farmers from pre-compiled list |  |
| **Communities 1** | 225 | 5 | 9 squares (1km^2^) | 25 households (one member per household) |
| **Communities 2** | 350 | 10 | 14 squares (1km^2^) | 25 households (one member per household) |

- - - 1. Inclusion and exclusion criteria

Wastewater treatment plant workers, faecal sludge workers, farmer and community members will not be allowed to participate in the study if they do not fulfill any of the following exclusion criteria:

- too sick to attend school or participate in the study (e.g. severe diarrhoea, severe anaemia, high fever, etc.)
- absence of written informed consent
- person is younger than 18 years of age
  - - 1. Sample analysis

The collected stool samples will be transferred to the laboratory of the Vector Control Division of the MOH on the same day for examination of helminth eggs and intestinal protozoa cysts.

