3. **Socio-economic status:** to assess the socio economic status as potential confounding factor we will obtain information around the salary per month, amount of people living in the household and on property possession.
4. **Hygienic behaviour:** to assess personal hygienic behaviour as potential confounding factor we will ask questions around washing/showering and hand washing.
5. **Consumption of water and food:** to assess the consumption of contaminated food and water as potential confounding factor we will obtain information around: (i) consumption and treatment of drinking water from various sources; (ii) consumption and concerns of root and leaf crops; and (iii) if participant is undertaking any farming what kind of crops he/she is growing.
6. **Disease signs and symptoms:** to observe signs and symptoms of diseases participants experienced over the past 2 weeks we will ask questions: (i) about general diseases symptoms (headache, fever, abdominal pain, acute and chronic coughing, chest pain, loss of weight, nausea, vomiting), physical pains (back, joint and muscle pain) and injuries, (ii) we will ask more specific questions around water-washed infection to determine skin and eye diseases as defined in the ‘Oxford handbook of tropical medicine’ (Eddleston et al. 2012). For skin diseases we will also ask for the specific part of the location (e.g. arm and leg); and (iii) questions on diarrhoeal episodes (defined as three or more loose or liquid stools per day) experienced today, 48 hours ago, 7 days ago and 14 days ago. Additional questions will be asked in order to characterize the diarrhoea such as presence of blood and mucus.
7. **Risk perception:** to assess the awareness of the health risk due to the work and the exposure to wastewater and faecal sludge.
8. **Personal protective equipment (PPE) (only W1/W2 and F):** to assess the use, the compliance and the efficacy of specific PPE.
9. **Worker safety (only W1/W2 and F):** to assess the need for other PPE and measures/controls that should be in place for making the work safer.
10. **Stool collection:** At a this stage of our research we want to ask the participant if he/she is willing to provide a stool sample for assessing the burden of intestinal parasites (e.g. soil-transmitted helminth and intestinal protozoa). If yes, we would measure the weight and height to calculate the body mass index to provide the appropriate dose of treatment in case of positive laboratory analysis.

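### The farmer (F) v C2 odds ratio mixes wastewater exposure with farming itself, and the plan neither deliberately samples farmers without wastewater nor names farming as a confounder

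*Combined protocol and SAP*

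**What the plan says.** Section 1.4 and the approach under 4.2.1 contrast "directly exposed groups (worker and farmers) and partially and non-exposed groups (communities").

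The groups are defined in 4.2.1.1 and Table 3:
- **F:** "farmers working along the Nakivubo Channel and the wetland (F"). Table 3 adds that they are exposed to wastewater and/or faecal sludge.
- **C1:** "Community in proximity of the wetland but are no farmers". Section 4.2.1.1 words this more narrowly, as doing no farming within the wetland.
- **C2:** defined by living and working about 2 km from the swamp. Farming is neither required nor excluded. Table 6 draws "25 households (one member per household") per square.

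Section 4.2.1.2 ranks exposure in four levels, with "the second highest to F (due to accidentally intake of contaminated water and soil"). Section 1.3 states a causal aim, and 4.2.1.8.2 compares the groups by confounder-adjusted odds ratios. The confounders named in 4.2.1.6.2 are demographic factors, behaviour, water and crop consumption, and socio-economic status.

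In the questionnaire (4.2.1.7.2), chapter 2 asks occupation. Chapter 5 asks "if participant is undertaking any farming what kind of crops he/she is growing". Chapter 8 is headed "Personal protective equipment (PPE) (only W1/W2 and F"), and chapter 9 on worker safety has the same restriction.

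**The concern.** To attribute an excess in F to wastewater, F should be compared with people who resemble them apart from the wastewater. Here the comparison groups differ from F in two ways at once: they are not exposed in the same way, and most or all of them do not farm. The main helminth outcomes are soil-transmitted, so contact with soil, manure and animals through farming is a plausible separate route to infection. Covariate adjustment can separate the two only through those C2 members who happen to farm.

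F is 275 of 1000 participants. A raised F v C2 odds ratio would naturally be read as harm from wastewater. It would also be set against the simulated infection risks for farmers when the QMRA is validated (4.2.3.1).

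**Working it through.** **1. The plan's own figure.** Table 4, scenario 3, gives 20% in C2 and 32% in F. OR = (0.32/0.68)/(0.20/0.80) = 0.4706/0.25 = 1.88. An even log-odds ladder up to OR 2.5 for W1/W2 gives 2.5^(2/3) = 1.84, or 31.5% in F, which agrees after rounding.

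**2. What each group can identify.**

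| Group | Farms? | Wastewater/sludge exposure |
|---|---|---|
| W1/W2 | not specified | highest |
| F | all | second |
| C1 | none (Table 3) | third |
| C2 | by chance only | assumed none |

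The only people who farm without exposure are the chance farmers in C2. No planned analysis uses them.

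**3. What F v C2 shows if wastewater has no effect.** The documents give neither a farming OR (g) nor the share of C2 who farm (s). I assume g = 1.25, 1.5 or 2.0 and s = 5–20%, and keep C2 at 20% overall.

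- Solve (1−s)q + s·p = 0.20, where odds(p) = g·odds(q). Here q is the prevalence in non-farmers and p the prevalence in farmers.
- F v C2 OR = odds(p)/0.25.
- Probability of significance: two-sided 5% Wald test on the log OR, 275 in F, independent observations. C2 is taken as 225 (4.2.1.2) and as 350 (Table 6), because the two places disagree.

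Example, g = 1.5, s = 10%, C2 = 225: q = 0.1929, odds 0.2390; ×1.5 = 0.3585, so p = 0.2639. OR = 0.3585/0.25 = 1.434, ln OR = 0.3605, SE = 0.2156, z = 1.67, probability of significance 39%.

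| Farming OR (assumed) | F v C2 OR | Significant, C2 = 225 | Significant, C2 = 350 |
|---|---|---|---|
| 1.25 | 1.19–1.24 | 13–16% | 15–19% |
| 1.5 | 1.37–1.47 | 31–43% | 38–52% |
| 2.0 | 1.70–1.92 | 71–87% | 81–94% |

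The ranges run over s from 20% to 5%. In these studies the difference between F and C2 is real. The error lies in attributing it to wastewater.

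**4. Spill-over into the four-level trend.** Suppose only F is raised and the four levels are fitted as one trend (C2 300, C1 200, F 250, W 150). A farming OR of 1.25, 1.5 or 2.0 then gives an apparent W1/W2 v C2 trend OR of 1.12 (z 0.51), 1.24 (z 0.96) or 1.45 (z 1.72). A direct W1/W2 v C2 comparison does not use F and has no such spill-over.

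**5. Precision of F v C2 farmers without any quota.** The number of C2 farmers runs from 5% of 225 (11) to 20% of 350 (70). With 32% of 275 v 20% of n, the CI factor is exp(1.96·SE):
- n = 11: SE 0.765, factor 4.5
- n = 18: SE 0.603, factor 3.3
- n = 70: SE 0.326, factor 1.9

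**6. A quota of 100 farmers within C2.** SE 0.281, factor 1.74, power 61% at 32% v 20%. Finding 100 means screening about 100/0.20 = 500 to 100/0.05 = 2000 households. If these farmers are left out of W1/W2 v C2 (38.5% of 150 v 20%) and C2 is 225, 125 remain and power falls from 97% to 91%, before clustering or adjustment.

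**The case against.** The strongest reply is that little in the study depends on this contrast.

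- **Sizing.** Sample size rests on OR 2.5 between W1/W2 and C2, and F is an intermediate level. This stands, apart from the spill-over if a single trend is fitted.
- **Irrigation advice.** A reader might infer that it rests on F v C2. The documents do not support that: 4.2.3.2 derives the recommendations from simulation, using measured pathogen concentrations, literature dose–response data and exposure scenarios, with the survey as validation. Section 4.2.2.2 also compares pathogen sequences in wastewater and sludge with those in stool, and a sub-sample of Ascaris positives is typed as *A. lumbricoides* or *A. suum*. These safeguards are partial: they use subsamples, and the typing covers one parasite.
- **Questionnaire.** A reader might infer that farming goes unrecorded in the community groups. It does not: chapter 2 asks occupation and chapter 5 covers any farming. C2 must also work about 2 km away, so its farmers count as unexposed under the plan's assumption. The instrument is a separate document, so footwear or livestock items may already be in it.
- **Soil.** Contaminated soil is part of the exposure as the plan defines it (4.2.1.2, 4.2.3.1). Treating all soil contact as confounding would remove some of the effect of interest. This stands and limits the fix.
- **Size.** No document gives a farming OR. At 1.25 the problem is modest, and at 1.1 significance occurs in about 6–7% of studies, close to nominal. The wastewater example in 1.2, where "a study conducted on farmers who use wastewater in India had excess prevalence and intensity of infection compared to a control group", does not help, because the protocol does not say whether those controls farmed.

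**Conclusion.** The point holds for the farmer contrast. As planned, F v C2 cannot separate wastewater from farming, no group of farmers without wastewater is deliberately sampled, and farming, manure and livestock contact are not named confounders. A farming OR near 2.0 would by itself give about the planned 1.88. An OR of 1.25 would mislead in 13–19% of studies. The structural problem needs no particular value, but its size depends on the assumed farming OR and C2 farming share, with observations treated as independent.

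The consequence is limited to attributing the farmers' excess risk and to using F data to validate the QMRA. It would go too far to say that hypothesis 1 is invalidated, since the direct W1/W2 v C2 contrast is largely unaffected. It would also go too far to say that a farmer control group is indispensable, given its yield and cost in step 6.

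**What to change.** 1. **Questionnaire.** Keep the farming item in chapter 5. Ask about soil, manure and livestock contact, and use of footwear or gloves, in all five groups instead of asking about protective equipment only in W1/W2 and F. Record where soil contact takes place, so that contact with swamp or channel soil can be told apart from other soil.
2. **Analysis.** Add a sensitivity model for F with farming and these contacts as covariates. Do not adjust for contact with wastewater-contaminated soil, which is part of the exposure.
3. **Secondary estimate.** Report F v C2 farmers with its confidence interval and the number of C2 farmers. Expect about 11 to 70 of them, and an interval of the estimate times or divided by roughly 4.5 to 1.9.
4. **Wording.** State in 4.2.1.8.2, and where the QMRA is validated, that a raised F v C2 odds ratio cannot be attributed to wastewater alone.

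The cost is a few more questionnaire items and a weaker causal statement for farmers, with no extra participants. The items must be added before fieldwork.

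A farmer quota within C2 is optional. If the investigators want one, they should weigh 61% power with 100 farmers against the extra screening and the possible loss in W1/W2 v C2. They should first reconcile the C1 and C2 sizes, which 4.2.1.2 and Table 6 give in opposite order.
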